### Procedures

The study involves a total of 2 or 3 visits (Figure 2). The initial visit 1 is a screening clinic appointment that may take place at any time of day. During this visit, participants provide written informed consent and are evaluated for study eligibility, including an in-office automated blood pressure measurement. SBP will be measured using the OMRON BP7450 (OMRON Healthcare, Inc) which automatically takes 3 measurements separated by 1 minute and provides the mean result. This device, which is supplied by the sponsor, will be used at each site, and site staff will be trained on its use. The clinical conditions for measuring blood pressure will follow the recommendations of the AHA and Centers for Disease Control and Prevention.^3^^,^^23^ Additional data collected at the initial visit include demographics, concurrent illnesses, history of cardiovascular diseases, and medical and medication history, including assessment of medication adherence. Physical measurements (height, weight, and waist circumference) are recorded, and a nonfasting blood sample is collected for laboratory assessments, including dehydroepiandrosterone sulfate, plasma renin activity, aldosterone levels, and a complete metabolic panel (Table 2). All enrolled participants with rHTN attend visit 2 within 2 weeks of visit 1, arriving at 8 AM (±1 hour) fasted for 8 or more hours and having taken a 1-mg oral dose of dexamethasone the night before (at 11 PM ±1 hour). Fasting blood samples are collected to assess cortisol, ACTH, glucose, and lipid levels (Table 2).

**Figure 2 fig2:**
[figure not shown]
**Flow of Participants in the MOMENTUM Study** The study involves a total of 2 or 3 visits. At the initial screening visit assessing eligibility, participants will undergo an in-office automated blood pressure measurement and have a blood sample taken for nonfasting laboratory tests. All enrolled participants with resistant hypertension attend visit 2 having taken a 1-mg oral dose of dexamethasone the night before for hypercortisolism assessment (primary endpoint). Participants with a post-DST cortisol level of >1.8 μg/dL attend visit 3 for a nonfasted morning blood draw to test ACTH and cortisol levels and scheduling of a noncontrast adrenal CT scan. ^a^Plasma renin activity, aldosterone, dehydroepiandrosterone sulfate, N-terminal-pro-brain natriuretic peptide, hemoglobin A1c, fibrosis-4, aspartate aminotransferase-to-platelet-ratio index, uric acid, high-sensitivity C-reactive protein, complete blood count, comprehensive metabolic panel, estimated glomerular filtration rate, creatinine/cystatin-C, and urine albumin-to-creatinine ratio. ^b^The dexamethasone level must be ≥140 ng/dL for the DST to be valid. For participants with dexamethasone levels <140 ng/dL, the test may be repeated with 4 mg dexamethasone. ^c^ACTH, fasting glucose, and fasting lipids. ACTH = adrenocorticotropic hormone; CT = computed tomography; DST = dexamethasone suppression test.

**Table 2 tbl2:** Clinical Laboratory Variables Evaluated During the MOMENTUM Study by Clinic Visit

Visit 1: nonfasting; any time of day	
Hematology	Red blood cell count, distribution, and width; hematocrit; hemoglobin, mean corpuscular hemoglobin, mean corpuscular hemoglobin volume, and mean corpuscular volume; platelet count and mean platelet volume; white blood cell count; neutrophils;^a^ lymphocytes;^a^ monocytes;^a^ eosinophils;^a^ basophils^a^
Serum chemistry	Sodium, potassium, calcium, chloride, phosphorus, magnesium, creatinine, cystatin-C, creatine kinase, bilirubin (total and direct), albumin, alkaline phosphatase, lactate dehydrogenase, AST, ALT, blood urea nitrogen, uric acid, bicarbonate, total protein, eGFR_creatinine_, eGFR_cystatin-C_
Pituitary/adrenal hormone levels	DHEAS, plasma renin activity, aldosterone
Glucose control	HbA1c
Inflammatory markers	High-sensitivity C-reactive protein
Natriuretic peptide	NT-proBNP
Liver fibrosis	FIB-4, APRI
Urinalysis	UACR, urine pregnancy test for women of reproductive potential
Visit 2: fasting; 8 AM (dexamethasone taken prior evening)	
Pituitary/adrenal hormone levels	Serum cortisol, reflex dexamethasone levels for participants with post-DST cortisol >1.8 μg/dL, plasma ACTH
Glucose levels	Serum glucose
Lipid metabolism	Total cholesterol, low-density lipoprotein-cholesterol, high-density lipoprotein-cholesterol, very low-density lipoprotein-cholesterol, triglycerides
Visit 3: 8 AM (for subjects with post-DST cortisol >1.8 ug/dL)	
Pituitary/adrenal hormone levels	Plasma ACTH, serum cortisol

ACTH = adrenocorticotropic hormone; ALT = alanine aminotransferase; APRI = aspartate aminotransferase-to-platelet-ratio index; AST = aspartate aminotransferase; DHEAS = dehydroepiandrosterone sulfate; DST = dexamethasone suppression test; eGFR = estimated glomerular filtration; FIB-4 = fibrosis-4; HbA1c = hemoglobin A1c; NT-proBNP = N-terminal-pro-brain natriuretic peptide; UACR = urine albumin-to-creatinine ratio.

a Percent and absolute.

Participants with a post-DST cortisol level of ≤1.8 μg/dL are informed of their normal cortisol level, and no additional visits are required. Participants with a post-DST cortisol level of >1.8 μg/dL attend visit 3 within 2 weeks of the receipt of the DST result. Visit 3 entails a nonfasted morning blood draw to test ACTH and cortisol levels and scheduling of a noncontrast adrenal computed tomography scan. The total study duration is anticipated to be <4 weeks for most participants. Further clinical workup for participants with post-DST cortisol >1.8 μg/dL and potential treatment of the hypercortisolism is not mandated within the study. Rather, it will follow the local standard of care at each participating site.

Safety data (ie, adverse events, laboratory test results, and physical findings) are collected throughout the study, and patients are monitored on an ongoing basis. As this is a noninterventional study, an adverse event is defined as any unfavorable or unintended event related to a study procedure, such as a blood draw or imaging procedure, that occurs during the study.

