### Outcomes

The study’s primary endpoint is the prevalence of endogenous hypercortisolism in a population with rHTN. Endogenous hypercortisolism is defined as a cortisol level of >1.8 μg/dL after a 1-mg overnight DST with adequate concomitant dexamethasone levels (≥140 ng/dL). The dexamethasone level cutoff of 140 ng/dL, rather than the Endocrine Society–recommended cutoff of 220 ng/dL,^13^ is based on the normal range of the assay used in the central laboratory for the study (ARUP Laboratories). Dexamethasone is measured by a validated liquid chromatography with tandem mass spectrometry method with assay validation according to Clinical and Laboratory Standards Institute guidance under College of American Pathologists/Clinical Laboratory Improvement Amendments regulations. The threshold of 140 ng/dL corresponds to the lower reference limit of dexamethasone observed in the control population used to validate the assay and is concordant with reference intervals reported by other clinical reference laboratories. For participants with dexamethasone levels <140 ng/dL, the DST can be repeated using a 4-mg dose. If the dexamethasone level does not reach ≥140 ng/dL after repeat testing, the test is considered invalid, and the data are not included in the primary endpoint analysis.

Secondary endpoints include assessment of clinical and laboratory characteristics associated with an increased likelihood of endogenous hypercortisolism, proportion of individuals with markers of hyperaldosteronism and other causes of hypertension, and proportion of individuals with endogenous hypercortisolism and rHTN who have abnormal adrenal imaging. Exploratory endpoints include assessment of the proportion of participants with post-DST cortisol levels of 1.2 to 1.8 μg/dL and those with levels <1.2 μg/dL and their associated clinical and laboratory characteristics.

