### Statistical methods

The primary endpoint (prevalence of endogenous hypercortisolism in participants with rHTN) will be analyzed using descriptive statistics, with proportions and 95% CIs reported. All enrolled participants who meet the eligibility criteria and have a valid DST result will be included. Statistical analyses will use all available data without any imputation. Secondary endpoints will be summarized with descriptive statistics and 95% CIs. Clinical and laboratory findings will be evaluated for associations with endogenous hypercortisolism. Medical history will be coded using Medical Dictionary for Regulatory Activities v27 or later and presented by system organ class and preferred term. Descriptive statistics and 95% CIs will also characterize participants with markers of primary hyperaldosteronism (plasma renin activity and aldosterone) with and without endogenous hypercortisolism, those with primary hyperaldosteronism, endogenous hypercortisolism and rHTN, and those with endogenous hypercortisolism and rHTN with and without abnormal adrenal imaging. Continuous variables will be summarized by sample size (nonmissing), mean, SD, median, minimum, and maximum. Categorical variables will be summarized as numbers and percentages of participants in each category. Based on the CATALYST study,^15^ a sample size of approximately 1,000 participants is expected to provide a robust estimate of endogenous hypercortisolism prevalence, assuming a prevalence result in the range of 10 to 25%.

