### Study limitations

Limitations of the study include that rHTN was determined based on a one-time in-office blood pressure measurement and investigator judgment as to participant adherence with at-home blood pressure checks and blood pressure medications. To address this limitation, in-office blood pressure was assessed in a consistent manner using the same in-office automated blood pressure device. Blood pressure was measured 3 times automatically, with a 1-minute interval between each measurement, without the investigator present. The mean blood pressure was used to determine eligibility. Out-of-office blood pressure measurements were reviewed with each participant to support the investigator in ensuring participants met the eligibility criteria. Similarly, adherence to blood pressure medications was based on participant interviews and investigator judgment. To minimize confounding of the DST results, the inclusion and exclusion criteria were carefully designed to rule out the most common confounding factors, including exogenous glucocorticoid exposure, oral contraceptive use, and specific comorbidities. Attainment of adequate dexamethasone levels was also ensured.

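### Dexamethasone is assayed only when cortisol exceeds 1.8 μg/dL, so the validity rule can exclude only non-suppressors and entry to the primary analysis depends on the outcome

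*Protocol article*

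**What the plan says.** - **Measurement.** The Visit 2 block of Table 2 lists serum cortisol and ACTH, and then "reflex dexamethasone levels for participants with post-DST cortisol >1.8" μg/dL. The Procedures section, listing what the Visit 2 fasting bloods are for, names cortisol, ACTH, glucose and lipids but not dexamethasone. Participants at or below 1.8 μg/dL are told their cortisol is normal and have no further visit.
- **Validity.** Figure 2, footnote b: "The dexamethasone level must be ≥140 ng/dL for the DST to be valid". The footnote is not limited to participants with high cortisol.
- **Repeat.** Outcomes: "For participants with dexamethasone levels <140 ng/dL, the DST can be repeated using a 4-mg dose". The repeat is optional. If the level is still too low afterwards, "the test is considered invalid, and the data are not included in the primary endpoint analysis".
- **Analysis set.** Statistical methods: "All enrolled participants who meet the eligibility criteria and have a valid DST result will be included", and "Statistical analyses will use all available data without any imputation".
- **Assurance.** Study limitations: "Attainment of adequate dexamethasone levels was also ensured".

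**The concern.** These statements do not fit together. A participant whose cortisol suppresses never has a dexamethasone level, so cannot be shown to meet the validity condition, yet must be in the denominator if a prevalence is to be estimated. Once suppressors are admitted without a level, the condition can act only on people whose cortisol is already above the diagnostic cut-off. Low-dexamethasone non-suppressors leave both numerator and denominator. Low-dexamethasone suppressors stay in as negatives. Whether a participant can be excluded is then decided by the variable that defines the outcome.

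The primary result is a single proportion, which the Conclusions hope may inform guidelines. Its binomial interval covers sampling error only and says nothing about the removed participants.

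Two further statements are affected. The sentence on adequate dexamethasone in Study limitations has no support for suppressors, who are most of the sample at the planned prevalence of 10% to 25%. The exploratory groups with cortisol of 1.2 to 1.8 and below 1.2 μg/dL both lie under the reflex trigger. Visit 2 yields no dexamethasone level for either, so a difference in drug exposure between them cannot be examined.

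**Working it through.** **Inputs from the article (Statistical methods):** N of about 1,000; assumed prevalence 10% to 25%; 95% CI. No precision target is stated, so there is no planned figure to reproduce beyond the implied half-width.

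**Assumed inputs (the article gives neither):**
- d = share of participants with dexamethasone still inadequate after any repeat, taken as 5%, 10% and 15% and independent of disease.
- f = share of low-dexamethasone non-cases whose cortisol fails to suppress, taken as 0, 0.5 and 1.
- Low-dexamethasone cases are assumed not to suppress.

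**Step 1. Implied precision.** Half-width = 1.96 × √(p(1 − p)/1000).
- p = 0.25: 1.96 × √(0.1875/1000) = 2.68 points.
- p = 0.10: 1.96 × √(0.09/1000) = 1.86 points.

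**Step 2. Effect of excluding only non-suppressors.** With true prevalence π, the excluded share is d[π + (1 − π)f], and the cases retained are π(1 − d). So

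reported prevalence = π(1 − d) / {1 − d[π + (1 − π)f]}.

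Example: π = 0.25, d = 0.10, f = 0 gives 0.225/0.975 = 23.08%.

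| True π | d | f = 0 (all low-dexamethasone non-cases suppress) | f = 0.5 | f = 1 (none suppress) |
|---|---|---|---|---|
| 25% | 5% | 24.05 (-0.95) | 24.52 (-0.48) | 25.0 (0) |
| 25% | 10% | 23.08 (-1.92) | 24.00 (-1.00) | 25.0 (0) |
| 25% | 15% | 22.08 (-2.92) | 23.45 (-1.55) | 25.0 (0) |
| 10% | 5% | 9.55 (-0.45) | 9.77 (-0.23) | 10.0 (0) |
| 10% | 10% | 9.09 (-0.91) | 9.52 (-0.48) | 10.0 (0) |
| 10% | 15% | 8.63 (-1.37) | 9.26 (-0.74) | 10.0 (0) |

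Entries are the reported prevalence in percent, with the shift in points in brackets. Under the same model, applying the rule to everyone whatever their cortisol would return π.

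**Step 3. Bounds without the model.** Take 250 non-suppressors among 1,000, of whom 40 are unresolved (illustrative counts):
- Plan: (250 − 40)/(1,000 − 40) = 210/960 = 21.9%.
- Unresolved all counted as non-cases: 210/1,000 = 21.0%.
- Unresolved all counted as cases: 250/1,000 = 25.0%.

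The planned figure is above one bound and below the other. Its own half-width is 1.96 × √(0.21875 × 0.78125/960) = 2.6 points, giving about 19.3% to 24.5%. In this example the upper bound falls just outside that interval.

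**The case against.** The intended analysis can be inferred. Outcomes attaches adequate dexamethasone to the definition of a case, suppressors are told their result is normal, and the Eligibility criteria show that the worry is false-positive tests. A reflex assay in non-suppressors fits that aim, and a suppressed cortisol is a defensible negative even if the drug level was low. This stands, and the fix below adopts it. It also disposes of a stronger inference a reader might draw from footnote b taken literally: that only non-suppressors have a valid test and the reported prevalence would approach 100%. Nobody can intend that.

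On size, the case against is also fair. The largest shifts need every low-dexamethasone non-case to suppress, in which event low exposure never causes a false positive and the validity rule would serve no purpose. With half suppressing, every shift in the table is inside the CI half-width. Even when all suppress, only the 15% row at 25% prevalence exceeds it. The unresolved share is unknown, and the optional repeat may make it small.

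It can be said that handling of unresolved tests belongs in the analysis plan, which the article says will be signed off before analysis. That would answer a complaint about missing detail. Here, however, the article itself states the measurement rule, the validity rule and the analysis set, and they conflict. Accepting suppressors as negatives does not cure the one-sided exclusion, and the article does not say how a low level with no repeat is classified.

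The sentence on adequate levels could be read as covering positive results only. It is loosely worded rather than demonstrably false.

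**Conclusion.** The point holds as an internal conflict with a consequence for the primary estimate. On the only workable reading, exclusion for low dexamethasone is open to non-suppressors alone.

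If low dexamethasone is independent of disease, the reported prevalence is too low or unbiased. At a true 25% the shift is 0 if all low-dexamethasone non-cases fail to suppress, -0.5 to -1.6 points if half suppress, and -0.95 to -2.9 points if all suppress, against a half-width of 2.7. At a true 10% it is 0 to -1.4 points against 1.9. All of this rests on an assumed 5% to 15% unresolved.

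A reader might infer that the design inflates prevalence or that a large bias has been shown. The documents support neither: under the independence model the shift is never upward, and its size depends on a rate they do not give. Without that model the direction is open, because unresolved participants could be mostly cases or mostly non-cases. What is firm is that the planned interval leaves this uncertainty out.

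**What to change.** 1. Reconcile Outcomes, Figure 2 footnote b, Table 2 and Statistical methods by defining the primary set as all eligible participants with a post-DST cortisol, classified as:
   - negative: cortisol ≤1.8 μg/dL, with no dexamethasone level needed;
   - positive: cortisol >1.8 μg/dL with dexamethasone ≥140 ng/dL;
   - unresolved: cortisol >1.8 μg/dL without an adequate level, including a low level with no repeat.
2. Report the number unresolved. Beside the planned figure, give the prevalence with unresolved participants kept in the denominator and counted all as non-cases and all as cases.
3. Limit the Study limitations sentence on adequate dexamethasone to participants in whom it was measured.
4. State that the exploratory comparison of cortisol 1.2 to 1.8 with <1.2 μg/dL has no dexamethasone data.

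The cost is a wording change, a few table rows and a wider stated uncertainty around the headline figure. It can be settled before the analysis plan is signed off. Assaying dexamethasone in samples from suppressors would allow a direct check, but the article does not say that serum is kept. That step is optional and not part of the required change.

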### Statistical methods

The primary endpoint (prevalence of endogenous hypercortisolism in participants with rHTN) will be analyzed using descriptive statistics, with proportions and 95% CIs reported. All enrolled participants who meet the eligibility criteria and have a valid DST result will be included. Statistical analyses will use all available data without any imputation. Secondary endpoints will be summarized with descriptive statistics and 95% CIs. Clinical and laboratory findings will be evaluated for associations with endogenous hypercortisolism. Medical history will be coded using Medical Dictionary for Regulatory Activities v27 or later and presented by system organ class and preferred term. Descriptive statistics and 95% CIs will also characterize participants with markers of primary hyperaldosteronism (plasma renin activity and aldosterone) with and without endogenous hypercortisolism, those with primary hyperaldosteronism, endogenous hypercortisolism and rHTN, and those with endogenous hypercortisolism and rHTN with and without abnormal adrenal imaging. Continuous variables will be summarized by sample size (nonmissing), mean, SD, median, minimum, and maximum. Categorical variables will be summarized as numbers and percentages of participants in each category. Based on the CATALYST study,^15^ a sample size of approximately 1,000 participants is expected to provide a robust estimate of endogenous hypercortisolism prevalence, assuming a prevalence result in the range of 10 to 25%.

### Ethics and data sharing

The study is being conducted in accordance with Institutional Review Boards, local regulations, and ethical principles based on the Declaration of Helsinki and consistent with the International Conference on Harmonisation guidelines for good clinical practice. Participants must provide written informed consent before study-specific screening procedures. Participant confidentiality is maintained through multiple measures, including the use of unique participant identifiers on all study records. The study is funded and sponsored by Corcept Therapeutics Incorporated, Redwood City, California. The sponsor is responsible for the study design, trial oversight, data collection, and analysis. The statistical analysis plan will be prespecified and signed off before data analysis. The authors retained full editorial control and final responsibility for all content in this manuscript. No data are available for sharing at this time. On trial completion, deidentified data sets for the results from this trial may be made available to qualified researchers following submission of a methodologically sound proposal to [contact]. Data will be made available for such requests following the online publication of the primary results and for 1 year thereafter in compliance with applicable privacy laws, data protection, and requirements for consent and anonymization. Data will be provided by Corcept Therapeutics Incorporated.

## Discussion

Hypercortisolism is associated with adverse clinical consequences, particularly cardiovascular disease, as evident at any level of elevated cortisol.^24^, ^25^, ^26^, ^27^ In endogenous hypercortisolism, hypertension and thromboembolic events occur in up to 85% and 20%, respectively, of such individuals.^20^^,^^24^^,^^28^, ^29^, ^30^ Beyond vascular disease, endogenous hypercortisolism is associated with a broad spectrum of cardiometabolic complications, including insulin resistance, hyperglycemia, diabetes, fatty liver/metabolic dysfunction-associated steatotic liver disease, dyslipidemia, and visceral obesity, increasing the risk of cardiovascular morbidity and mortality.^20^^,^^29^^,^^31^ Individuals with endogenous hypercortisolism have an elevated risk of myocardial infarction and cardiac failure.^24^ Furthermore, cardiovascular disease is a leading cause of death in this population.^32^, ^33^, ^34^

The substantial burden of rHTN establishes an urgent need for greater understanding of its causes, which help inform new treatment strategies. Endogenous hypercortisolism can cause hypertension through direct and indirect mechanisms, including metabolic, vascular, renal, and cardiac action.^11^^,^^24^^,^^25^^,^^35^ In the renin-angiotensin system, excess cortisol induces increased hepatic synthesis of angiotensinogen, whereas renin may be low or suppressed, suggesting dysregulation of angiotensin receptor signaling. Although angiotensin II levels may be normal, the number of angiotensin II type 1 receptors is increased, resulting in enhanced response to angiotensin II and promoting vasoconstriction.^11^^,^^25^^,^^35^ In the vasoregulatory system, hypercortisolism may elevate levels of the vasoconstrictor endothelin-1 and impair the production of vasodilators, including prostacyclin and kallikreins, worsening endothelial dysfunction.^11^^,^^25^^,^^35^ Sustained increases in cortisol also downregulate nitric oxide synthase expression and inhibit nitric oxide signaling.^11^^,^^25^ In the sympathetic nervous system, excess cortisol enhances the pressor response to β-adrenergic agonists.^35^ Hypercortisolism increases sodium/hydrogen exchanger 3 activity in the proximal tubule, increasing renal sodium reabsorption, a main contributor to hypertension pathophysiology and the rationale for diuretic use in treating rHTN.^36^^,^^37^ Excess cortisol may exceed the capacity of 11β-hydroxysteroid dehydrogenase type 2 to convert cortisol to inactive cortisone, promoting higher cortisol levels and mineralocorticoid receptor activation.^11^^,^^35^^,^^38^ Notably, cortisol binds the mineralocorticoid receptor as avidly as aldosterone and can be present in 100- to 1,000-times higher plasma concentrations, expanding plasma volume through sodium retention.^11^^,^^38^

Other recognized secondary causes of rHTN include primary aldosteronism, renal parenchymal disease, and renal artery stenosis.^2^ Several of these, particularly aldosteronism, are part of the AHA guideline recommendations for routine screening in rHTN.^2^ European Society of Cardiology and Endocrine Society Clinical Practice guidelines recommend screening for primary aldosteronism in all adults with hypertension.^39^^,^^40^ Studies indicate up to 21% of patients with confirmed primary aldosteronism also have autonomous cortisol secretion.^31^^,^^41^ Although the AHA guidelines include endogenous hypercortisolism as a potential secondary cause of rHTN, routine screening is not recommended, reportedly due to lack of sufficient data.^2^

Few epidemiological studies have evaluated endogenous hypercortisolism in individuals with hypertension or rHTN. A 2025 systematic review identified 8 relevant studies published between 1977 and 2020, reporting endogenous hypercortisolism prevalence rates of 0% to 18.3% in individuals with hypertension.^42^ However, differences in testing approaches and definitions limited comparability, with only 1 study evaluating rHTN specifically. A 2012 study from Brazil involving 423 individuals reported that 27% of those with rHTN (defined by the same AHA criteria as in MOMENTUM) had endogenous hypercortisolism (based on 1-mg overnight DST).^22^ The CATALYST study demonstrated a 36.6% prevalence of endogenous hypercortisolism in individuals taking ≥3 blood pressure–lowering medications, although conducted in a population with T2D.^15^ To our knowledge, no study to date has investigated endogenous hypercortisolism in a U.S. population with rHTN.

MOMENTUM seeks to advance our understanding of the prevalence of endogenous hypercortisolism in a population with rHTN. These findings could support broader screening and more targeted treatment. Currently, diagnosis of endogenous hypercortisolism is often delayed for years.^19^^,^^20^^,^^43^ These delays may contribute to adverse clinical outcomes, as both the duration and the level of exposure to excess cortisol activity are significantly associated with increased morbidity and mortality risk.^19^^,^^20^^,^^26^^,^^43^, ^44^, ^45^ Although not assessed in this study, treatments for endogenous hypercortisolism are available, and more therapies are in development.^45^, ^46^, ^47^ In this context, MOMENTUM may help identify individuals with rHTN who could benefit from available and emerging therapies.

